### Study design

After obtaining informed written consent, all required measurements will be performed at the beginning of the study. Then, stratified block randomization will be done based on the type of cancer (colon or rectum) and BMI (≤23, > 23) using the www.randomization.com website. The statistician will fold the paper containing a randomization number and put them in the envelopes and write the code on them. The envelopes will be kept at the enrollment center. Then, for each qualified patient, the nutritionist randomly picks one of the envelopes after shuffling and allocates patients into control and intervention groups. It is not possible to blind study participants or staff in this study due to nutritional interventions. Nevertheless, the outcome assessor will be blinded to the group assignment.

Regarding colorectal cancer treatment, subjects with rectal cancer undergoing first-line radiotherapy and subjects with colon cancer undergoing first-line chemotherapy with capecitabine and oxaliplatin (CAPOX), 5-fluorouracil-leucovorin-irinotecan (FOLFIRI), 5-fluorouracil and oxaliplatin (FOLFOX), or capecitabine will be included [17]. As explained, people will be placed in separate blocks based on the type of cancer. The duration of the study for both intervention and control groups will be 8 weeks. Participants in the intervention group will receive a Mediterranean diet menu along with extra virgin olive oil, while participants in the control group will receive nutritional advice for cancer patients and dietary recommendations for weight gain. To assess participants’ adherence to the proposed diets, a 1-day food record will be used in the second, fourth, sixth, and eighth weeks of the study. Moreover, to encourage patients to follow the diet, all patients will be contacted weekly during the study. Participants will be asked to maintain their normal daily activities during the study. In addition, individuals’ physical activity will be monitored through completing a 1-day record in the second, fourth, sixth, and eighth weeks of the study. At the end of the study, all required measurements will be taken again in both groups. A Standard Protocol Items: Recommendations for Interventional Trials (SPIRIT) diagram for the trial schedule is indicated in Fig. 2.

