### Assessment of study outcomes

In the current study, the main primary outcome would be nutritional status, fat-free mass, muscle strength, and inflammatory markers including interleukin-6 (IL-6), tumor necrosis factor-alpha (TNF-α), and high-sensitive C-reactive protein (hs-CRP). Moreover, the following variables will be considered as the secondary outcome: serum albumin and total protein, complete blood count (CBC), and quality of life. All primary and secondary outcomes will be assessed at the beginning and end (the eighth week) of the study.

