#### Nutritional status assessment

The nutritional status of individuals will be evaluated by the Patient Generated-Subjective Global Assessment Questionnaire (PG-SGA) [22]. This questionnaire assesses patients’ nutritional status based on information about a person’s medical history and diet history (weight change, food intake, gastrointestinal problems, and physical function) as well as clinical symptoms (body fat loss, muscle loss, and edema). According to the guidelines of the PG-SGA questionnaire, the severity of malnutrition will be defined in three following levels: scores between 0 and 1 indicate well-nourished status (A), scores between 2 and 8 indicate moderate or suspected malnutrition status (B), and scores of ≥ 9 indicate severe malnutrition status (C).

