### Sample size calculation

The sample size required for the current study was calculated using the formula (*n* = 2 [(*z*1−*α*/2 + z1−*β*)^2^ · *s*^2^]/*d*^2^), which has been proposed for parallel clinical trials [24]. Considering the nutritional status (score obtained from the PG-SGA questionnaire) as the key variable [25], type I error of 5% (*α* = 0.05), type II error of 20% (*β* = 0.20, study power = 80%), standard deviation of PG-SGA score (*S*= 4.1), and *d* as equal to 3.9 [25], the required sample size for each group will be 17 patients. However, to ensure a sufficient sample size at the end of the study and taking into account the 15% probable dropout, 20 patients in each group will be recruited according to the inclusion criteria. Considering that the samples will be given in this project are among the patients referred to the radio-oncology clinic and introduced by the radio-oncology specialist, therefore, while ensuring the correct selection of samples based on the inclusion criteria, the number of patients is sufficient to reach the desired sample size for this research project.

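### With outcomes taken only at baseline and week 8, and missing values replaced by a mean, dropout that follows a patient's mid-trial course is poorly handled

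*Protocol article*

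**What the plan says.** On timing, the Protocol article (Assessment of study outcomes) says "All primary and secondary outcomes will be assessed at the beginning and end (the eighth week) of the study", and the Abstract agrees. Under Study design, "The duration of the study for both intervention and control groups will be 8 weeks".

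Between those two points the trial is in touch with patients. Under Study design, "all patients will be contacted weekly during the study", "a 1-day food record will be used in the second, fourth, sixth, and eighth weeks of the study", and physical activity is followed by "completing a 1-day record in the second, fourth, sixth, and eighth weeks of the study". The Intervention section adds that controls are followed up like the diet arm.

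The Sample size calculation is built on the PG-SGA score, and 20 per group are recruited "taking into account the 15% probable dropout". According to Nutritional status assessment, the score combines "medical history and diet history (weight change, food intake, gastrointestinal problems, and physical function") with examined signs, "as well as clinical symptoms (body fat loss, muscle loss, and edema").

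Under Statistical analysis, missing values are replaced by the mean of the variable concerned. The planned analyses are repeated measures ANOVA and ANCOVA on baseline.

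**The concern.** A patient who worsens and leaves between baseline and week 8 contributes no post-baseline PG-SGA. Replacing the missing value with a mean assigns that patient an average result, whatever led to the loss.

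The protocol's own text makes such losses plausible. The Discussion describes a population whose nutritional status keeps falling. The Exclusion criteria list death, a change of feeding route, a change of treatment and unwillingness to continue. They also list low adherence to the Mediterranean diet, a reason that by its wording concerns only the diet arm, so losses need not be alike in the two arms. If the diet arm loses the patients who are doing badly and the control arm loses patients at random, those remaining at week 8 make the diet look better than it is. Three losses among 20 per arm is enough for this to matter.

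**Working it through.** **1. The plan's own figures.** Inputs from Sample size calculation: two-sided alpha 0.05, power 80%, S = 4.1, d = 3.9.

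n = 2 × (1.960 + 0.842)² × 4.1² / 3.9² = 17.35 per group. The protocol states 17. Then 17 / 0.85 = 20, as stated. So 15% dropout means 3 of 20 per arm, 6 of 40 in all.

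**2. Size of bias by simple arithmetic.** Bias in the completers' difference = missing share × the extra amount by which one arm's lost patients differ from its completers, compared with the other arm. That extra amount is assumed.

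| Extra shift (points) | Bias = 0.15 × shift | Share of 3.9 |
|---|---|---|
| 2 | 0.30 | 8% |
| 4.1 (one SD) | 0.62 | 16% |
| 8.2 (two SD) | 1.23 | 32% |

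These are before baseline adjustment.

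**3. Bias left after baseline ANCOVA.** Large-sample simulation of normal scores at baseline, week 4 and week 8. From the protocol: SD 4.1, 15% dropout per arm, effect 3.9. Assumed: correlation 0.5 with baseline, 0.6 to 0.7 between week 4 and week 8, a week-4 effect of 2.5 when the week-8 effect is 3.9, diet-arm dropout depending on the week-4 score (log-odds 1 to 2 per SD), control dropout random. Negative values favour the diet.

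- True effect 0: completers' ANCOVA gives about -0.2 to -0.4.
- True effect -3.9: it gives about -4.1 to -4.3.

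As a share of d: 0.2 / 3.9 = 5% and 0.4 / 3.9 = 10%.

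**4. Which extra data help.** A second simulation, true effect -3.9. Assumed correlations: baseline with week 8 0.5, baseline with interim 0.6, interim with week 8 0.75, food record with week 8 0.5. Dropout is again informative in the diet arm only.

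| Diet-arm dropout depends on | Completers, unadjusted | ANCOVA on baseline | Baseline + food record | Baseline + interim PG-SGA |
|---|---|---|---|---|
| Baseline PG-SGA | -4.25 | -3.90 | -3.89 | -3.89 |
| Interim PG-SGA | -4.44 | -4.23 | -4.15 | -3.90 |
| Unseen week-8 value | -4.62 | -4.45 | -4.37 | -4.25 |

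Baseline adjustment is enough in the first row. In the second, the food record helps a little, and a fully observed interim score removes the bias. In the third, every option leaves some.

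**5. The stated mean replacement.** The protocol does not say whether the mean is taken by arm or overall.

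- By arm: the unadjusted completers' difference is unchanged. The SD falls to 4.1 × √(16/19) = 3.76 and the apparent SE to 3.76 × √(2/20) = 1.19, against 4.1 × √(2/17) = 1.41 from 17 observed per arm, a ratio of 0.85.
- Overall: the difference is multiplied by about 0.85, for example 0.85 × 4.44 = 3.77, whatever the reason for dropout.

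Neither uses the patient's own course.

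**The case against.** The strongest case against is that nothing here is a mistake. Two assessments over 8 weeks contradict nothing in the protocol, ANCOVA on baseline is already planned, and the bias is small: 0.2 to 0.4 points is 0.14 to 0.28 of an unadjusted SE of 1.41. It needs informative dropout in one arm only, and every correlation is assumed. The mode of weekly contact is not stated, so one cannot say that a questionnaire there costs no visit. Only the outcome assessor is blinded, so staff taking interim scores may know the allocation. Enrolment began in January 2022, so an amendment reaches only some of the 40 patients. All of this stands, and it limits the point to an improvement. It does not rescue mean replacement, which makes no use of records the trial already holds.

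Four stronger readings are tempting and are not supported:

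- **That no analysis can recover informative dropout.** Baseline ANCOVA handles loss explained by baseline, the food and activity records are post-baseline data in both arms, and a delta analysis can bound the rest.
- **That an interim score removes the bias in every case.** It does so when dropout depends only on that score and the score is seen for everyone lost. A patient leaving in week 3 has no week-4 value, and the history items alone are less than the full score simulated above.
- **That the same mechanism in both arms understates the effect.** When each arm is calibrated to 15% dropout, no such bias appears.
- **That averaging weeks 4 and 8 buys precision.** The variance ratio [(1 + r)/2 - r²] / (1 - r²) is 0.615, 0.667 and 0.706 at r = 0.3, 0.5 and 0.7. With assumed effects of 2.5 and 3.9, however, the averaged effect is 3.2. Then 3.2/√ratio = 4.08, 3.92 and 3.81 against 3.9, a change of about +5%, 0% and -2%.

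**Conclusion.** The point holds as a modest weakness in how losses are handled, not as an error in the visit schedule. With one post-baseline outcome, 15% expected dropout and mean replacement, loss that follows a patient's mid-trial course is poorly dealt with.

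The likely size is 0.2 to 0.4 PG-SGA points in favour of the diet. This rests on the assumed correlations, on dropout driven by week-4 status in the diet arm alone, and on a completers' ANCOVA as the comparator. The protocol's mean replacement behaves differently: it either overstates precision or shrinks the difference.

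The conclusion would seldom turn on this. For an observed difference of 3.9 with SE 1.41, significance is lost only at a differential shift of (3.9 - 1.96 × 1.41) / 0.15, about 7.6 points. The case for acting is that the remedy is cheap and that interim scores not collected now cannot be obtained later.

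**What to change.** 1. Replace mean imputation with multiple imputation, or a likelihood-based analysis of week 8, using baseline PG-SGA and the week 2, 4 and 6 food and activity records from both arms. With about three losses per arm, keep the model small, for example one energy-intake summary per patient. This needs no new data and covers patients already enrolled.
2. For patients still to be followed, add the patient-reported PG-SGA history items at the week 2, 4 and 6 contacts in both arms, as auxiliary data only. Keep the full, blinded PG-SGA at week 8 as the endpoint.
3. Bound what remains with a delta-adjusted sensitivity analysis, and state separately how deaths enter the comparison, since no interim score defines an outcome after death.

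Cost: a change to the analysis text, a short amendment, and a few minutes of patient time per contact. Downsides: the interim score is partial, may be collected by unblinded staff, and is available only for patients not yet past those weeks.

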#### Anthropometric assessment

Height will be assessed using a tape measure in a standing position when the person without shoes and heels will close to the wall from the back, the knees will be straight and without bending, and the patient will be looking straight ahead and the eyes will level with the ears, and he will be asked to breathe slowly. Height was recorded with an accuracy of 0.1 cm. Handgrip strength, which is an indicator of muscle strength, will be measured using a digital dynamometer (Seahan, model SH5003, Seahan Co, South Korea). Body composition, including body fat percentage (PBF), body fat mass (BFM), fat-free mass (FFM), soft lean mass (SLM), body mass index (BMI), base metabolic rate (BMR), waist to hip ratio (WHR), and total body water (TBW), will be measured by the bio-electrical impedance analysis (BIA) (model: Portable Jawon medical). To get accurate results, the patient will be asked to be well hydrated, have not exercised in the past 6 h, and have not consumed caffeine, alcohol, or diuretics in the previous 24 h.

#### Nutritional status assessment

The nutritional status of individuals will be evaluated by the Patient Generated-Subjective Global Assessment Questionnaire (PG-SGA) [22]. This questionnaire assesses patients’ nutritional status based on information about a person’s medical history and diet history (weight change, food intake, gastrointestinal problems, and physical function) as well as clinical symptoms (body fat loss, muscle loss, and edema). According to the guidelines of the PG-SGA questionnaire, the severity of malnutrition will be defined in three following levels: scores between 0 and 1 indicate well-nourished status (A), scores between 2 and 8 indicate moderate or suspected malnutrition status (B), and scores of ≥ 9 indicate severe malnutrition status (C).

#### Biochemical assessment

In the fasting state, a 10-mL venous blood sample will be taken from each patient at the beginning and end of the trial. After separating the serum by centrifugation, the samples are stored at −80°C. Inflammatory factors (hs-CRP, IL-6, TNF-α) will be measured using the enzyme-linked immunosorbent assay (ELISA) by the use of commercially available kits. Serum albumin and total protein will be measured using an autoanalyzer (spectrophotometric method). The complete blood count (CBC) will also be done through a cell counter.

#### Assessment of other variables

General information about age, gender, education, economic status, medical history, medication and supplement use, and history of COVID-19 will be assessed by standard questionnaires. The quality of life of individuals will be assessed using the European Organization for Research and Treatment of Cancer quality of life questionnaire (EORTC QLQ-C30) (third edition) prepared by the European Agency for Research and Treatment of Cancer [23]. The validity and reliability of the questionnaires have already been evaluated in Iran [23]. In addition, the side effects of intervention as well as the treatment patients are taking such as diarrhea, nausea, constipation, vomiting, and appetite of patients will be assessed using the relevant items in this questionnaire. Also, the functional status of patients at the beginning and end of the study will also be assessed according to the Karnofsky scale. Participants will be asked to provide four 1-day food records throughout this trial. After providing the food records, the frequency of each food item will be converted to grams per day by considering the household measures of portion sizes. The daily energy and nutrient intake of each participant will be calculated by using Nutritionist IV software which is a modified food composition database based on the US Department of Agriculture.

### Data management

Special forms were designed by the researcher that were completed at any point in time and entered into the local database within a week of completion. Completed documentation is stored in a locked cabinet, with access to the principal investigator of the study. Forms are identified by a unique participant ID number and do not contain identifiable patient information. Data-driven queries are generated in the database daily, including date, range, and logic checks. Moreover, a list of all outcome data will be provided for patients who discontinue or deviate from study protocols. After collecting data, to ensure the data are complete and accurate, data will be double check by supervisors.

### Data monitoring

The Steering Committee of the university will oversee the project’s implementation and progress. The quality of the work, the patient admission process, and the data review will be carefully monitored by the University’s Executive Committee. If any changes are necessary for the continuation of the intervention or if the physician determines that the intervention should be stopped, the patient or his/her guardian will be informed of changes or discontinuation of the diet. Concerning the auditing plan, the progress and results of the study will be assessed by the University’s Steering Committee every 3 months. Moreover, the trial’s process and results will be independent of investigators and the sponsor.

### Sample size calculation

The sample size required for the current study was calculated using the formula (*n* = 2 [(*z*1−*α*/2 + z1−*β*)^2^ · *s*^2^]/*d*^2^), which has been proposed for parallel clinical trials [24]. Considering the nutritional status (score obtained from the PG-SGA questionnaire) as the key variable [25], type I error of 5% (*α* = 0.05), type II error of 20% (*β* = 0.20, study power = 80%), standard deviation of PG-SGA score (*S*= 4.1), and *d* as equal to 3.9 [25], the required sample size for each group will be 17 patients. However, to ensure a sufficient sample size at the end of the study and taking into account the 15% probable dropout, 20 patients in each group will be recruited according to the inclusion criteria. Considering that the samples will be given in this project are among the patients referred to the radio-oncology clinic and introduced by the radio-oncology specialist, therefore, while ensuring the correct selection of samples based on the inclusion criteria, the number of patients is sufficient to reach the desired sample size for this research project.

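### The stated formula gives 17.35 per group and was rounded down to 17, so the 17 expected completers give about 79% power (about 77% by a t-test), not quite 80%: a minor slip

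*Protocol article*

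**What the plan says.** The section on sample size calculation in the protocol article sizes the trial on the PG-SGA score. It prints the formula n = 2(z₁₋α/₂ + z₁₋β)²s²/d² per group, "which has been proposed for parallel clinical trials". The inputs are a type I error of 5%, a type II error of 20%, a standard deviation of 4.1 and a difference d taken "as equal to 3.9".

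It concludes that "the required sample size for each group will be 17 patients" and then, "taking into account the 15% probable dropout, 20 patients in each group will be recruited". That makes 40 patients in all.

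The section on statistical analysis plans repeated measures ANOVA, and an analysis of covariance of the changes with baseline values as covariates. The sample size section does not tie its power figure to either analysis, and the article gives no baseline-to-week-8 correlation.

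**The concern.** A required sample size is the smallest whole number that reaches the target power. If the formula returns a fraction above 17, then 17 does not reach the target and the next integer is needed. The dropout allowance is built on 17 and comes out at exactly 20, so it leaves no slack to absorb the rounding.

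The formula also uses normal quantiles. With about 17 patients per group these are somewhat optimistic compared with a t-test.

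What is at stake is the accuracy of a stated figure. Anyone can recompute the 80% from the printed inputs and will find slightly less.

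**Working it through.** **Inputs**, all from the sample size section: two-sided alpha 0.05 (z = 1.960), power 80% (z = 0.8416), s = 4.1, d = 3.9, dropout 15%.

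**1. The protocol's own formula.**

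n = 2 × (1.960 + 0.8416)² × 4.1² / 3.9² = 2 × 7.849 × 16.81 / 15.21 = **17.35**.

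With z-values rounded to 1.96 and 0.84 the result is 17.33. Either value rounds up to 18. The stated 17 is what rounding to the nearest integer, or down, gives.

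**2. Dropout step.**

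- From 17: 17/0.85 = 20.0, as stated, and 20 × 0.85 = 17 completers.
- From 18: 18/0.85 = 21.2, so 22 per group, or 44 in total.

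**3. Power by the protocol's normal approximation.** For n per group, power ≈ Φ(d/(s√(2/n)) − 1.960). At n = 17, 3.9/(4.1 × √(2/17)) = 2.773, and Φ(2.773 − 1.960) = Φ(0.813) = 79.2%.

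**4. Power by a t-test** of an unadjusted difference (noncentral t, 2n − 2 degrees of freedom), beside the normal figure:

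| n per group | Normal approximation | t-test |
|---|---|---|
| 17 | 79.2% | 76.7% |
| 18 | 81.4% | 79.2% |
| 19 | 83.4% | 81.4% |
| 20 | 85.3% | 83.4% |

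The smallest n reaching 80% is 18 by the protocol's formula and 19 by the t-test.

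**5. Difference detectable with 80% power at 17 per group.**

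- Normal formula: (1.960 + 0.8416) × 4.1 × √(2/17) = 3.94 points.
- t-test: 4.06 points.

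The assumed difference is 3.9.

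**6. Effect of baseline adjustment, under assumption.** Suppose 4.1 is the SD of the score itself and r is its correlation between baseline and week 8. Neither is fixed by the article. ANCOVA then multiplies the variance by 1 − r². At 17 per group:

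| Assumed r | Normal approximation | Noncentral t, 31 df |
|---|---|---|
| 0.3 | 82.8% | 80.4% |
| 0.5 | 89.3% | 87.3% |

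Power returns to 80% at r of about 0.14 by the normal approximation and about 0.28 by noncentral t.

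**The case against.** The strongest reply is that the gap is negligible. On the protocol's own method it is 80 − 79.2 = 0.8 points. The SD and the difference are printed to one decimal. If they were themselves rounded, SDs of 4.05 to 4.15 and differences of 3.85 to 3.95 give n between about 16.5 and 18.2, so the excess of 0.35 lies within the precision of the inputs. This stands as a statement of size. It does not make 17 the result of the figures as printed.

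A second reply is that the t-test is not the planned outcome analysis. The statistical analysis section uses it for baseline comparisons and plans repeated measures ANOVA and ANCOVA for the outcomes. That is fair. The normal formula is a common approximation, and sizing on the unadjusted variance is usually conservative. A reader might infer that leaving out baseline adjustment is a further error, or that the detectable difference is 4.06 by the protocol's own method. The documents support neither: the omission is a normal choice, and the protocol's formula gives 3.94. The 76.7% is useful only as a small-sample check on an unadjusted comparison.

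A third reply is that ANCOVA restores the power. It may well do so, but this cannot be stated as fact. It needs a correlation the article does not give, and it needs 4.1 to be the SD of the score, not of its change. The repeated measures interaction, with two time points, amounts to a t-test on change scores. With 4.1 as the SD at both visits, its power at 17 per group would be about 62%, 77% and 93% at assumed correlations of 0.3, 0.5 and 0.7.

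Nor does the 85.3% at 20 per group answer the point. It needs 20 observed outcomes, while the plan expects 17. Replacing missing values by the variable's mean, as the analysis section plans, adds no information about the treatment effect.

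**Conclusion.** The point holds as a minor arithmetic slip. The protocol's formula and inputs give 17.35, so 18 per group is the smallest number that reaches 80%, not 17. The 17 completers expected from 20 per group give about 79% power by the protocol's normal formula and about 77% by a t-test for an unadjusted difference of 3.9. The first figure needs only the printed inputs and the planned 15% dropout; the second replaces normal quantiles with t quantiles.

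A reader might go further and conclude that the trial is underpowered or must be enlarged to 44 patients. The documents do not support that. The shortfall is one completer per group, the dropout step is correct, and the planned ANCOVA is expected to raise power, by an amount that cannot be fixed from the article.

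**What to change.** Keep 40 patients and restate the power along these lines: *20 randomised per group, with 17 expected at week 8, give about 79% power by the normal approximation (about 77% by a t-test) for an unadjusted difference of 3.9 with SD 4.1.*

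Optionally, add that the planned baseline-adjusted ANCOVA is expected to raise power. Any figure should be labelled as an assumption: for example, if 4.1 is the SD of the score, about 80% at a baseline correlation of 0.3 and about 87% at 0.5 (noncentral t).

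The cost is one sentence and a slightly less favourable stated power. It needs no extra patients and no change of design, so it can be made while enrolment continues.
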